## Abstract

**Background:**

There is a need for evidence of the effectiveness of pre-operative exercise for patients undergoing major cancer surgery; however, recruitment to such trials can be challenging. The PrE-operative Physical Activity (PEPA) Trial will establish the feasibility and acceptability of a pre-operative exercise programme aimed to improve patient outcomes after cytoreductive surgery and pelvic exenteration. The secondary aim is to obtain pilot data on the likely difference in key outcomes (post-operative complications, length of hospital stay, post-operative functional capacity and quality of life) to inform the sample size calculation for the substantive randomised clinical trial.

**Methods/design:**

Twenty patients undergoing cytoreductive surgery and pelvic exenteration at the Royal Prince Alfred Hospital, Sydney will be recruited and randomly allocated (1:1 ratio) to either 2 to 6 weeks’ pre-operative exercise programme (intervention group) or usual care (control group). Those randomised to the intervention group will receive up to six individualised, 1-h physiotherapy sessions (including aerobic and endurance exercises, respiratory muscle exercises, stretching and flexibility exercises), home exercises (instruction and recommendations on how to progress the exercises at home) and encouragement to be more active by using an activity tracker to measure the number of steps walked daily. Patients allocated to the control group will not receive any specific advice about exercise training. Feasibility will be assessed with consent rates to the study, and for the intervention group, retention and adherence rates to the exercise programme. Acceptability of the exercise programme will be assessed with a semi-structured questionnaire. The following measures of the effectiveness of the intervention will be collected at baseline (2 to 6 weeks pre-operative), a week before surgery, during hospital stay and pre hospital discharge: post-operative complication rates (Clavien-Dindo), post-operative functional capacity (Six-minute Walk Test) and quality of life (SF-36v2®) and length of hospital stay. Functional status will be additionally measured using Cardiopulmonary Exercise Testing (CPET), at baseline and within a week before surgery.

**Discussion:**

The PEPA Trial will provide important information about the feasibility and acceptability of a pre-operative exercise programme for patients undergoing major cancer surgery. Data from the PEPA Trial will be used to inform the design, methodology and to calculate sample size required for a larger, definitive trial.

**Trial registration:**

Australian New Zealand Clinical Trials Registry, ID: ACTRN12617001129370. Registered on 1 August 2017.

**Electronic supplementary material:**

The online version of this article (10.1186/s13063-018-2481-2) contains supplementary material, which is available to authorized users.

## Background

For people with major advanced primary or recurrent gastrointestinal malignancies, surgery to achieve complete removal of the tumour, with or without neo-adjuvant or adjuvant chemotherapy, offers the best chance of cure [1, 2]. Major, advanced primary or recurrent gastrointestinal malignancies collectively are the most lethal cancers worldwide. They are also some of the leading causes of disease burden in Australia and some of the most expensive cancers to treat [3]. The burden of these major advanced primary or recurrent malignancies is explained by the complexity and extension of these radical procedures; with some having a treatment cost of around AU$137,000; most of this cost is associated with the extended length of stay in hospital due to the high number of complications [4, 5].

One intervention that holds potential to reduce post-operative complications is a pre-operative exercise programme to improve patients’ fitness before surgery [6, 7]. A recent systematic review of pre-operative exercise interventions for patients undergoing cancer surgery [8] found 17 reports of 13 different trials investigating the effectiveness of exercise in six oncological procedures: colon (one trial, *n* = 42) [9], colorectal liver metastasis (one trial, *n* = 38) [10, 11], oesophageal (two trials, *n* = 98) [12–14], lung (six trials, *n* = 434) [15–21], oral (one trial, *n* = 60) [22] and prostate cancer (two trials, *n* = 134) [23, 24]. While for most cancer procedures only reports of small single trials were found, pre-operative exercise in patients undergoing surgery for lung cancer was shown to reduce the risk of post-operative complications by 48%, and reduced the length of hospital stay by 3 days when compared to no treatment control or minimal intervention. Interestingly, no information on cost and quality of life outcomes were reported.

In other patient groups, promoting physical activity in the pre-operative period appears promising to improve functional capacity and facilitate post-operative recovery [25]. Given that the surgical work-up period for most patients who have major advanced primary or recurrent gastrointestinal cancer is approximately 4 to 8 weeks, there is opportunity to incorporate an exercise programme into the pre-operative preparation period without the need to delay surgery.

Therefore, the *primary aims* of this pilot randomised controlled trial are to determine: (1) the feasibility of incorporating a standardised, intensive exercise programme into the pre-operative period for patients undergoing cytoreductive surgery or pelvic exenteration at Royal Prince Alfred Hospital (RPAH), Sydney; (2) the acceptability of the exercise programme to patients and (3) the acceptability to patients of being randomised to the exercise programme or usual care. The *secondary aim* is to obtain pilot data on the likely difference in key outcomes (post-operative complications, length of hospital stay, post-operative functional capacity and quality of life) to inform the sample size calculation for the substantive randomised clinical trial.

Our hypothesis is that the pre-operative exercise programme in combination with usual care is feasible and acceptable for patients undergoing cytoreductive surgery and pelvic exenteration.

## Methods/design

The PrE-operative Physical Activity (PEPA) Trial is a two-arm, pilot randomised controlled trial. The design of the trial is shown in Fig. 1. This protocol has been prepared according to the Standard Protocol Items: Recommendations for Interventional Trials (SPIRIT) Statement [26, 27] and will be reported according to the Consolidated Standards of Reporting Trials (CONSORT) Statement [28], and is registered at ANZCTR (ACTRN12617001129370). The SPIRIT Checklist is provided in Additional file 1 and the SPIRIT Diagram is included in Fig. 2.

**Fig. 1 Fig1:**
[figure not shown]
PEPA Trial design

**Fig. 2 Fig2:**
[figure not shown]
Details of the schedule of enrolment, interventions and assessments according to the Standard Protocol Items: Recommendations for Intervention Trials (SPIRIT) Diagram

A total of 20 patients will be randomly assigned via concealed allocation to receive: (1) a pre-operative exercise programme and usual care (intervention group) or (2) usual care alone (control group). To reduce participant burden, this study will use clinical data collected by the Pelvic Exenteration Surgery Quality and Improvement (PESQI) (Protocol No X13–0283 and HERC/13/RPAH/371) and the Peritonectomy Surgical Research Programme (PREMIER) (Protocol No X16–0482 and HREC/16/RPAH/691). Ethical approval for the PEPA Trial was obtained by the Sydney Local Health District Human Research Ethics Committee (Protocol No X17–0189 and HREC/17/RPAH282).

### Setting and participants

All consecutive patients undergoing cytoreductive surgery or pelvic exenteration at the RPAH and attending consultation rooms 2 to 6 weeks prior to their operation will be invited to participate by their treating surgeon.

### Eligibility criteria

The inclusion and exclusion criteria are listed below:

Inclusion criteria: to be eligible for the study, patients will have to be adults aged 18–80 years:Undergoing elective cytoreductive surgery or pelvic exenterationPresent to the participating gastrointestinal surgeon at least 2 weeks prior to planned surgery

Exclusion criteria: patients will be excluded from the study if they have:Cognitive impairment such that they are unable to provide informed consentCo-morbidity preventing participation in exercise (i.e. major cardiac, respiratory or musculoskeletal disease)Inadequate English language to the complete outcome measuresCurrent participation in an active exercise programme similar to the proposed interventionUnable to attend the exercise programme (e.g. living in another state)

Eligible patients will be provided with the Participant Information Sheet and the Participant Consent Form from their participating surgeon, who will explain the study aims and the practicalities of the exercise programme and data collection. Once informed consent has been obtained, the participating surgeon will forward the signed Participant Consent Form with the patients’ contact details to the study’s research officer who will contact the patient to organise a meeting for baseline assessment and randomisation. Patients will be reassured that their participation in the study will not alter their treatment pathway and that they can withdraw from the study at any time.

### Randomisation and allocation concealment

A research officer not involved in the trial will prepare the group allocation after written informed consent and baseline assessment are obtained. Randomisation will be carried out on a 1:1 basis and will utilise a computer-based, random-sequence generator, stratified by surgical procedure (cytoreductive surgery or pelvic exenteration). Consecutively numbered, sealed, opaque envelopes containing group allocation will be prepared by a researcher officer not involved in the trial. The concealed envelopes will be stored in a locked cabinet and will be opened in sequence to reveal group allocation by a research officer not involved in the recruitment process, treatment, or assessment of outcomes.

## Treatments

### Intervention group: pre-operative exercise and usual care

The exercise programme will consist of 60-min individualised (one-to-one) training session with a registered physiotherapist, once a week, for 2 to 6 weeks (maximum of six sessions). The exercise programme will be tailored to each patient based on a health assessment, taking into consideration patients’ current health status, physical activity level, presence of co-morbidities and medical history. Each session will consist of 10 min of warm-up exercises, 40 min of aerobic and endurance, respiratory and muscle-strength exercises, and 10 min of cool-down activities. The aerobic and endurance exercises will be performed at 12 to 14 on the rated perceived exertion scale (Borg Scale) [29] and the strength training will be performed at an intensity of 40% to 60% of the 1-repetition maximum (Table 1). Participants will be given instructions and recommendations on how to progress the exercises at home (four sessions of 60 min each per week at home). In addition to home exercises, patients will be encouraged to be more active by using an activity tracker (Fitbit™) that will be used to provide real-time feedback about their daily physical activity goals. Patients will be asked to report on a daily basis the number of steps per day and number of home exercises performed during the entire pre-operative period. Home exercises and number of steps will be captured in a daily exercise diary that participants will complete until the end of the exercise programme.

**Table 1 Tab1:**
[figure not shown]
Supervised pre-operative exercise programme (2 to 6 weeks)^a^

^a^The content of the programme will be subject to individual variability and will be adjusted to the individual patient as required

### Control group: usual care

The usual-care group will receive the routine care throughout their cancer pathway, from diagnosis to surgical resection and not take part in any formal exercise programme. No specific advice about exercise training will be offered.

### Study measures

Study data will be assessed at baseline (pre-operative), during the week before surgery (1 week pre-operative), intra-operatively, 10 days post-operative and pre hospital discharge (Fig. 2).

Participating surgeons will record clinical information (including intra-operative complications) on a standardised study data collection form. Baseline and follow-up outcome measures will be collected either by a research officer or by the study physiotherapist who will be blinded to group allocation. All pre- and post-operative treatments (e.g. chemoradiotherapy) for participants in both groups will be recorded by a research officer using a standardised form. The intra-operative data is already collected for all RPAH patients by the Pelvic Exenteration Surgery Quality and the Improvement (PESQI) research programme (Protocol No X13–0283 and HERC/13/RPAH/371) and the Peritonectomy Surgical Research Programme (PREMIER) (Protocol No X16–0482 and HREC/16/RPAH/691).

### Outcome measures

The PEPA Trial will collect the following information (Fig. 2):Demographic and clinical characteristics: prior to surgery (baseline), patients’ height and weight (kg), date of birth, gender, address, and type of cancer will be obtained from the PESQI and PREMIER databasesPhysical assessment: the physical assessment will be performed by the study physiotherapist and will be collected at baseline, within a week before the surgery, 10 days post-operative and pre hospital discharge. The following outcomes will be assessed:*International Physical Activity Questionnaire-Short Form (IPAQ-SF)*: self-reported physical activity will be measured using the IPAQ-SF [30]. The IPAQ-SF will be used to calculate the metabolic equivalent (MET) minutes per week spent in walking, in moderate and vigorous activities and the total MET minutes per week. The amount (minutes per day and number of days per week) of walking, moderate activity and vigorous activity recorded by the IPAQ-SF will be multiplied by a weighting (3.3 for walking, 4 for moderate activity and 8 for vigorous activity) to calculate MET minutes per week in each activity, and these values will be summed to produce the total MET minutes per week. Sedentary behaviour will be determined based on time spent sitting per day (minutes). In addition, participants will be categorised as achieving a low, moderate, or high physical activity level*Six-minute Walk Test (6MWT)*: the 6MWT will be conducted in accordance with the protocol of the American Thoracic Society. Participants will be instructed to walk as quickly as possible for 6 min up and down a 30-m, straight, indoor corridor. Standardised encouragement will be given each minute during the test. Oxygen saturation, heart rate and the distance walked will be recorded [31]*Isometric Quadriceps Strength Assessment*: quadriceps strength will be measured using a hand-held dynamometer [32]. Patients will be assessed in a sitting position with the knees and hips at 90°. Maximal voluntary contraction force (reported in kilograms) will be assessed as the best of three reproducible manoeuvres*Five Times Sit to Stand Test*: lower-limb strength and function will be measured using the Five Times Sit to Stand Test [33]. Patients will sit with arms folded across the chest and with their back against a chair. Patients will be instructed to stand up and sit down five times as quickly as possible. Time taken to complete the test will be recorded by the physiotherapist*Cardiopulmonary Exercise Test (CPET)*: the CPET will be conducted using a computer-controlled, electromagnetically braked cycle ergometer (Ergoline VIAsprint 200P, Germany) in accordance with the American Thoracic Society/American College of Chest Physicians (ATS/ACCP) statement [34]. maximal oxygen uptake (VO_2_ max; ml/kg/min) and anaerobic threshold (ml/kg/min) will be recorded at baseline and within a week before the surgery3.Clinical outcomes: clinical outcomes will be collected intra-operatively and post-operatively from PESQI and PREMIER databasesComplication rates: will be defined as the total number of complications post-operative and will be reported according to the Clavien-Dindo classification of surgical complications [35]Length of hospital stay: will be defined as the duration of inpatient hospital stay with the day of surgery considered as day 04.Quality of life, the Exercise Self-Efficacy Scale, the Depression, Anxiety, Stress Scale, and Participants views and satisfaction: quality of life will be measured by the Short Form 36 version 2 (SF-36v2®, Australian English) [36] at baseline, within a week before the surgery, 10 days post-operative and at pre hospital discharge. Exercise self-efficacy (measured with the Exercise Self-efficacy Scale) [37] and depression, anxiety, stress (measured with the Depression, Anxiety, Stress Scale) [38] will be assessed at baseline. Participants’ views and satisfaction with the study intervention will be assessed at pre hospital discharge

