### Blinding

Research officers involved in data collection will be blinded to group allocation. Due to the nature of the intervention, it will not be possible to blind participants and the physiotherapist delivering the pre-operative exercise intervention. However, the physiotherapist conducting the physical assessments in both groups and the surgeon will be blinded to participant group allocation and participants will be asked not to disclose group allocation to their physiotherapist assessor and surgeon. In addition, the statistician performing the statistical analyses will be blinded to group allocation.

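### The IPAQ-SF sits inside the blinded physiotherapist's assessment, which puts assessor blinding at avoidable risk for the secondary functional outcomes

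*Protocol article*

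**What the plan says.** In the Protocol article, Outcome measures, the physical assessment is one block of work given to one person: "the physical assessment will be performed by the study physiotherapist and will be collected at baseline, within a week before the surgery", and again ten days after surgery and before discharge. Five measures are listed under it: the IPAQ-SF, the 6MWT, quadriceps strength by hand-held dynamometer, the Five Times Sit to Stand and the CPET. For the first, "self-reported physical activity will be measured using the IPAQ-SF", from minutes per day and days per week of walking, moderate and vigorous activity. The other questionnaires (SF-36v2, exercise self-efficacy, depression/anxiety/stress, satisfaction) form a separate item that is not assigned to the physiotherapist.

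The Blinding section states that "the physiotherapist conducting the physical assessments in both groups and the surgeon will be blinded to participant group allocation". It supports this by asking patients to keep their group from that assessor and from the surgeon, and the Discussion relies on the same safeguard. Study measures adds that outcome measures may be collected by a research officer or by the blinded study physiotherapist.

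Intervention patients receive a supervised "training session with a registered physiotherapist, once a week, for 2 to 6 weeks", and at home "four sessions of 60 min each per week at home". For controls, "No specific advice about exercise training will be offered".

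**The concern.** The person who must stay unaware of the arm is given, within the same assessment, an instrument that measures what the intervention sets out to change. The visit in the week before surgery is the sensitive one: the programme is under way or just finished, and the arms differ most by prescription. A patient can obey the request not to name the group and still give an honest account of activity that points to it.

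Three of the tests run by this assessor leave room for tester influence. The 6MWT involves spoken encouragement, the dynamometer is held by the tester, and the sit-to-stand is timed by the physiotherapist. Under Statistical analysis, between-group changes in functional capacity and strength are to feed the sample size of the later trial. A tester who suspects the arm could tilt those differences, and any suspicion could carry into the post-operative tests if the same person does them.

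**Working it through.** The article gives no figure on this point to reproduce: no SD, effect size or power calculation. The check has three parts.

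**1. Who handles the answers.** Study measures allows either a research officer or the physiotherapist to collect outcomes in general. Outcome measures is more specific: it names the physiotherapist for the physical assessment and puts the IPAQ-SF, alone among the questionnaires, inside it. Followed as written, the activity answers go to the tester. No sentence keeps them from the tester. The article does not state whether the form is self-completed or taken by interview, or the order of the measures.

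**2. How far the prescription separates the arms.** Inputs from the Intervention group section: four home sessions and one supervised session a week, 60 min each. Inputs from Outcome measures: weights of 3.3 (walking), 4 (moderate) and 8 (vigorous).

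- Prescribed time: 4 × 60 + 1 × 60 = 300 min/week.
- All scored as walking: 300 × 3.3 = 990 MET-min/week.
- All scored as moderate: 300 × 4 = 1,200 MET-min/week.
- All scored as vigorous: 300 × 8 = 2,400 MET-min/week.

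The 990 to 1,200 range assumes full adherence, every minute scored as walking or moderate activity, and no displacement of other activity. It is not a floor: of each supervised hour, 20 min are warm-up and cool-down, and the other 40 min are shared among aerobic, respiratory and strength work.

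**3. How well the total predicts the arm.** Assume normal totals with equal SD in both arms, 1:1 allocation, and a tester who guesses intervention above the midpoint between the arm means. The chance of a correct guess is Φ(δ / (2 × SD)), where δ is the between-arm difference; 50% means no information. The SDs are assumptions. Full adherence uses δ = 1,200, half adherence δ = 600.

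| Assumed SD (MET-min/week) | Full adherence | Half adherence |
|---|---|---|
| 500 | Φ(1.20) = 88.5% | Φ(0.60) = 72.6% |
| 1,000 | Φ(0.60) = 72.6% | Φ(0.30) = 61.8% |
| 2,000 | Φ(0.30) = 61.8% | Φ(0.15) = 56.0% |
| 3,000 | Φ(0.20) = 57.9% | Φ(0.10) = 54.0% |

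Every entry is above 50%, but only the smallest SD with full adherence comes near to identifying the arm. The calculation uses a single total. A tester who also saw the baseline form, or the pattern of days and minutes, would have more to go on.

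The resulting bias cannot be derived from the article. As illustration only: if awareness shifted the 6MWT by 10 to 30 m and the SD of change were 60 m, the bias would be 10/60 = 0.17 to 30/60 = 0.5 SD. With about 10 patients per arm the standard error of the difference would be 60 × √(2/10) = 26.8 m, so a shift of that size could not be told from chance.

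**The case against.** A reader might infer that blinding fails by design: that the physiotherapist interviews the patient about exercise and then runs the tests. The text does not support this. It says only that activity is self-reported, and a form filled in by the patient fits that wording. Being listed first does not fix an order, and Study measures leaves room for a research officer to collect measures. Mode, order and handling of forms are also details that a journal article often leaves to the full protocol or an assessor manual.

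Nor do the answers reveal the arm. As described, the items record amounts of activity and not its source. Controls may walk or exercise on their own account, and over most of the assumed range the guess is only moderately better than chance.

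Existing protection counts too. For the 6MWT, "Standardised encouragement will be given each minute during the test" under a published test protocol, dynamometry takes the best of three repeatable efforts, and the CPET runs on a computer-controlled ergometer. The primary outcomes, feasibility and acceptability, do not depend on a blinded tester.

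All of this limits the size of the point. What remains is that the article does not merely leave out a procedure: it assigns this questionnaire to the tester's assessment, while the only stated safeguard at that contact is a request that does not reach truthful answers on a required form. Standardised encouragement helps the 6MWT but does nothing for the tester-held dynamometer or the timed sit-to-stand.

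**Conclusion.** The point holds as a risk. The assignment of the IPAQ-SF to the blinded tester sends allocation-related information to that person at the visit where the prescribed contrast is largest. The contrast is 300 min/week, or about 990 to 1,200 MET-min/week under the best-case scoring assumptions above. The information is partial: about 54% to 88.5% correct guesses, depending on assumed SD and adherence.

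The exposure is confined to the secondary functional outcomes that depend on the tester and to the planning data drawn from them. The article does not establish that the tester is unblinded or that the results are biased by any given amount, and the primary conclusions of this pilot are not touched. It is a cheap improvement, not a flaw that undermines the trial. It is also separate from the Feasibility section's use of the same physiotherapist title for recording attendance: separating the treating and assessing roles would leave this route open.

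**What to change.** In Outcome measures, take the IPAQ-SF out of the physiotherapist's assessment and list it with the other questionnaires. State that:

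- the patient completes it alone, as a REDCap survey or on paper returned in a sealed envelope;
- it is done after the performance tests at each visit;
- the answers, including those from earlier visits, are withheld from the tester.

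The cost is a short wording change and a form in a database already in use, with no extra staff or visits. The downside is that some self-completed answers will be unclear or incomplete; someone other than the tester can query these. Trial status reports that randomisation had already begun, so the date of the change should be recorded, and the same procedure carried into the definitive trial.
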